### Intervention delivery and exercise design

The present study is a quality PE/PA intervention in which a resistance-based HIIT session is embedded in the first 6–10 min of regular PE and PA lessons, replacing traditional warm-up activities. The intervention will be delivered five times a week—three PE and two PA lessons—over twelve weeks (from school term 2, week 5 to week 16, March to June 2024). Throughout the intervention, PE teachers will coordinate and supervise the HIIT intervention, while the delivery will be accomplished by two student peer-coaches, selected by the PE teacher within each intervention class. The control group will maintain their traditional warm-up activities, such as light running and static stretching.

To ensure quality and effective implementation, the leading researcher will collaborate with the PE teachers and peer-coaches for delivering the intervention during the initial two weeks. Researchers will visit the school once per month to provide on-going support and guidance. Additionally, a training logbook at each intervention class will be maintained by the PE teachers to document aspects, such as attendance, dose delivered and received, and adverse events. These records will be sent to researchers on a weekly basis to ensure prompt feedback and communication. In cases where HIIT sessions are cancelled due to inevitable factors such as large school events or severe weather, participants will be encouraged to complete these sessions during alternative times (e.g., breaks). These additional sessions will be supervised by peer-coaches and will be recorded in the training logbook. The control group will take their regular PE and PA lessons as usual.

The HIIT sessions consist of body-weight resistance exercises (e.g., high knees, jumping jacks, burpees), selected based on relevant literature (33, 40). The session length will be progressively extended from 6 to 10 min over the 12 weeks, accounting for fitness adaptations. Within each session, the work-to-rest ratio will increase from 10 s: 20 s, to 15 s: 15 s, until 20 s: 10 s as the exercise progresses. Furthermore, participants will perform one exercise (e.g., jumping jacks) twice in a minute to avoid monotony while preventing frequent exercise changes, thereby 6, 8 and 10 different exercises will be completed as the intervention duration increases. Moreover, flexibility will be allowed for each HIIT session, enabling adaptations whenever necessary (e.g., higher/lower exercise intensity). The adaptations made will be recorded on the training logbook. The details regarding the exercises are presented in Table 1.

To facilitate the implementation process, several strategies will be employed, including:
(1)training workshops for participants, peer-coaches, teachers and research staff (Table 2);(2)providing participants with opportunities to choose music and exercises (from an exercise pool over the final 3 weeks of the intervention);(3)the opportunity to win a prize upon completion of the intervention for all participants.

**Table 2 T2:** Details of training workshops for participants, peer-coaches, teachers and research staff.

Subjects	Timing	Content
Participants (CON)	Two PE lessons (40 min)	(1) Introduction of the programme; (2) outcome measurements; (3) familiarisation of executive function tasks; (4) maintain daily life.
Participants (INT)	Two PE lessons (80 min)	(1) Introduction of the programme; (2) familiarisation of equipment (e.g., HR monitor), executive function tasks and HIIT exercises; (3) outcome measurements.
Peer-coaches	One PE lessons (40 min)	(1) HIIT performing and leading; (2) HIIT rescheduling and regulation.
PE teachers	60 min	(1) Introduction of the programme; (2) familiarisation of equipment (e.g., HR monitor); (3) HIIT exercises; (4) training logbook; (5) intervention delivery.
Research staff	60 min	(1) Outcome measurements; (2) data collection principles (e.g., SAAFE).

CON, control group; INT, intervention group; PE, physical education; HR, heart rate; HIIT, high-intensity interval training; SAAFE, the supportive, active, autonomous, fair, enjoyable principles.

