### Recruitment and allocation

An invitation letter will be sent to nearby secondary schools at Ningbo University. When schools express their interest, contacts will be initiated to elucidate the participation requirements. Upon agreement from the schools, invitations will be extended to head teachers and PE teachers of year 7, who will then present the study to students for recruitment. To be eligible for participation, students are required to submit signed assent forms along with signed consent forms from their parents/guardians. Students with health or medical conditions that would restrict their ability to engage in vigorous PA will be excluded from the study. The screening process will involve reviewing the medical examination reports submitted by the participants’ parents or guardians. Classes will be randomly allocated to either *PRO-HIIT* group or control group, via a computer-based random number generator by an independent researcher. The randomisation and allocation will take place after baseline assessment. The randomisation will be stratified by PE teacher, wherein each teacher's classes will be randomly assigned to either the intervention or control group.

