#### Process evaluation

A comprehensive process evaluation will be conducted for the *PRO-HIIT* intervention, which will be guided by the MRC process evaluation framework (27). The framework contains three domains, including implementation (i.e., fidelity, reach, recruitment and retention, dose delivered and adaptation), mechanisms of impact (i.e., mediators, dose received, unintended consequences and response) and context (i.e., barriers, facilitators, and contamination). The MRC framework, in conjunction with insights from a recent school-based HIIT review by Liu et al. (23), will guide the adaptation of process evaluation measures tailored specifically to *PRO-HIIT*, as detailed in Table 3.

**Table 3 T3:** Medical research council definition for process evaluation and its application to the *PRO-HIIT* intervention.

Measurements	MRC definition	Apply to *PRO-HIIT*	How
Implementation: The process through which interventions are delivered, and what is delivered in practice.			
Fidelity	The consistency of what is implemented with the planned intervention.	HIIT intensity.	HR and RPE
Reach	The extent to which a target audience comes into contact with the intervention.	Schools or participants contacted.	Recruitment
Dose delivered	How much intervention is delivered.	HIIT session length, frequency and intervention duration/sessions in the protocol.	Protocol
Recruitment & retention	NG	Number of participants who are randomised and completed the intervention.	Training logbook and outcome assessment
Adaptation	Alterations made to an intervention in order to achieve better contextual fit.	Changes being made to facilitate *PRO-HIIT*.	Training logbook and teachers’ focus group
Mechanisms of impact: The intermediate mechanisms through which intervention activities produce intended (or unintended) effects.			
Mediator	Intermediate processes which explain subsequent changes in outcomes.	Mediators (e.g., sex, baseline CRF and BMI) influencing the outcome assessment.	Data analysis
Dose received	NG	HIIT sessions participants performed.	Training logbook
Unintended consequences	NG	Adverse events or other unanticipated fairs recorded.	Training logbook
Response	How participants interact with a complex intervention.	Feedbacks from participants and teachers.	Focus group and questionnaire
Context: Factors external to the intervention which may influence its implementation, or whether its mechanisms of impact act as intended.			

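### Adverse events are recorded in a logbook kept at the intervention classes, and no record is described for the control classes, so the unintended-consequences result is a one-arm count without a comparator

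*Protocol article*

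**What the plan says.** Three places in the protocol article bear on harm recording.

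- **Intervention delivery and exercise design.** The article says that "a training logbook at each intervention class will be maintained by the PE teachers to document aspects". The purpose continues: "to document aspects, such as attendance, dose delivered and received, and adverse events". The logbook also takes in sessions made up outside lessons: "These additional sessions will be supervised by peer-coaches and will be recorded in the training logbook".
- **Process evaluation, Table 3, row on unintended consequences.** The item is "Adverse events or other unanticipated fairs recorded", and the training logbook is the only source given.
- **Control arm.** "The control group will take their regular PE and PA lessons as usual". HIIT takes the first 6 to 10 minutes of the same kind of lesson, "replacing traditional warm-up activities"; control classes keep their usual warm-up.

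On allocation, Recruitment and allocation adds: "The randomisation will be stratified by PE teacher".

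**The concern.** The article fixes where adverse events are written down, by whom, and which source the process evaluation will use. Each of these points to the intervention classes. Pupils in both arms have three PE and two PA lessons a week, so a fall, strain or illness during a lesson can happen in either arm. An event noted in a HIIT class may be due to HIIT or may be one that would have occurred anyway. The trial has a randomised control group that could help to separate the two, but the stated recording does not use it.

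At stake is how the unintended-consequences result can be read. The intervention asks 12–13-year-olds for maximal effort five times a week, led by pupil peer-coaches, and the Discussion says that little is known about feasibility at this frequency. Readers will look to the adverse-event count for reassurance or warning, and a one-arm count supports neither in relative terms.

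**Working it through.** **Plan's own figures.** The article gives no figure for adverse events. Its sample size (d = 0.31, 80% power, α = 0.05 two-sided) reproduces: the t-test calculation gives 164.3, rounded up to the stated 165 per group. This point does not depend on it.

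**Step 1. Is there another source for control classes?** Set side by side:

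- Table 2, control participants' workshop: introduction, measurements, practice on the cognitive tasks, keeping to daily life. No adverse-event reporting.
- Table 5, outcome measures: no harm item in either arm.
- Focus groups, pupils: drawn from intervention classes only.
- Focus groups, teachers: all PE teachers attend, but the listed topics are feedback on HIIT, continued use, barriers and facilitators.

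None describes a record of events in control classes.

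**Step 2. How many pupils and lessons are concerned?**

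- Focus groups: 2 peer-coaches + 2 other pupils = 4 per intervention class, n = 16 in total. 16 / 4 = 4 intervention classes, so 8 − 4 = 4 control classes.
- Sample size estimation: about 50 pupils per class. 4 × 50 = about 200 control pupils of 8 × 50 = 400.
- Lessons: 5 per week × 12 weeks = 60 per class; 60 × 4 = 240 control class-lessons of 480.

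**Step 3. What can a one-arm count show?** (Illustration only; the article gives no event rates.) Assume that 2% to 5% of pupils have a lesson-related event during 12 weeks of usual lessons, and that 10 of 200 HIIT pupils (5%) have one.

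- Expected background among 200 pupils: 0.02 × 200 = 4 to 0.05 × 200 = 10.
- Excess due to HIIT: 10 − 10 = 0 to 10 − 4 = 6 pupils.
- Risk ratio: 5% / 5% = 1.0 to 5% / 2% = 2.5.

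The one-arm count is 10 throughout this range.

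**Step 4. What would control records add?** Take 10/200 v 4/200, without adjustment for class clustering.

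- Difference: 5.0% − 2.0% = 3.0 percentage points; Newcombe 95% CI −0.8 to 7.1.
- Risk ratio 2.5: SE of log RR = √(1/10 − 1/200 + 1/4 − 1/200) = √0.34 = 0.583; 95% CI 2.5 × exp(±1.96 × 0.583) = about 0.80 to 7.8.

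The comparison becomes estimable but stays imprecise, and allowing for only four classes per arm would normally widen these intervals.

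**The case against.** The case on the other side has real weight.

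- **Purpose.** Adverse events enter only as a process-evaluation item, beside attendance, dose and adaptations. Safety is not a listed aim and no between-arm harm comparison is planned. A record of what happened during delivery serves that purpose. This stands, and it limits the importance of the point. It does not supply what is needed to attribute an event to HIIT.
- **Silence about the control arm.** A reader might infer that events in control classes will go unrecorded altogether. The article does not say so. It is a condensed text, and a school or the full protocol may provide for incident reports. What the article supports is narrower: it assigns recording to the intervention classes, names one source, and describes none for the control classes.
- **Scope of the logbook.** A reader might also infer that the count necessarily mixes in background events from whole lessons. The article does not settle whether the logbook covers the whole lesson or only the HIIT block. If only the block, much less background is mixed in, and the matching comparator is the control warm-up.
- **Limited gain.** Under the assumed counts, control records would still give intervals that include no difference, and teachers who know the allocation may look harder for events in HIIT classes. This stands, and it is why any comparison should be descriptive.
- **Same teachers in both arms.** This is inferred. Stratifying by teacher suggests it, but the number of teachers and of classes per teacher is not given, and the article adds only that each teacher's "classes will be randomly assigned to either the intervention or control group".

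**Conclusion.** The point holds in a limited form and is worth acting on. As stated, adverse events are collected through a logbook at the intervention classes, with no record described for the other 4 of 8 classes (about 200 of 400 pupils). The unintended-consequences result is then an uncontrolled count.

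The split into four and four classes is inferred from the focus-group numbers, and the pupil numbers rest on the average class size. The 2% to 5% background rate, the count of 10 and the risk ratios of 1.0 to 2.5 are assumptions for illustration; the conclusion does not need them.

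A reader might go further and take this as a threat to the trial's main result, or as evidence that HIIT harms are being missed. The documents support neither. The shuttle-run analysis does not use these data, and the logbook does provide for events in HIIT classes.

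**What to change.** 1. PE teachers make the same brief adverse-event entry for each timetabled PE and PA lesson in all eight classes, with one definition and one time window.
2. Each event is marked as falling in the opening HIIT or warm-up block, or later in the lesson. This gives a like-for-like comparison for the block and settles the scope of the logbook.
3. Report events by arm descriptively, with no formal test. Show events in make-up sessions separately, because those sessions have no control counterpart.
4. If data collection has ended (Table 1 places delivery in March to June 2024 and follow-up in September), label the logbook count as uncontrolled and draw no conclusion on relative safety.

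Cost: about 240 short entries for control lessons (60 per class), plus the timing mark in the existing logbook. No extra staff are needed, particularly if the same teachers hold classes in both arms. The downsides are added recording in a plan that elsewhere limits the load on PE teachers, and possible ascertainment bias because teachers know the allocation. Step 4 needs only a sentence in the report.

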## Methods and analysis

### Study design

The study is a multi-centre collaborative work conducted by University of Exeter and Ningbo University. Consolidated Standards of Reporting Trials (34) and Template for Intervention Description and Replication (35) checklists will be adopted for guidance and reporting. The *PRO-HIIT* study will employ a two-arm cluster-randomised controlled trial design, with an intervention group and a treat as usual control group. Clusters in this study are eight classes of secondary school students, located in Ningbo City, China. The intervention will be delivered five times per week, commencing at the beginning of the three PE and two PA lessons. The PA lessons serve as a complementary opportunity for students to engage in exercises of their choice on days when PE lessons are not scheduled. Assessments will occur at three time points: baseline (T1), immediate post-intervention (T2) and two-month post-intervention (T3), with T3 aligning with the initial two weeks of a new school term following a two-month unstructured summer holiday. Table 1 presents an overview of the schedule for recruitment, intervention delivery and outcome assessments.

**Table 1 T1:** Overview of the *PRO-HIIT* intervention.

Procedures		Recruitment & pre-intervention measurements				Intervention phase (12 weeks)												Post-intervention measurements			Summer holiday	Follow-up measurements	
	22–26 Jan	26 Feb–22 Mar				25 Mar–14 Jun												17–28 Jun		1–4 Jul	5 Jul–1 Sep	2–13 Sep	
	2023–2024 school term 1	2023–2024 school term 2																				2024–2025 school term 1	
	week 22	week 1	week 2	week 3	week 4	week 5	week 6	week 7	week 8	week 9	week 10	week 11	week 12	week 13	week 14	week 15	week 16	week 17	week 18	week 19		week 1	week 2
Eligibility screening		√																					
Consents & assents																							
Training workshop			√																				
Randomisation					√																		
Maturity				√																			
PA (GENEActiv)					√	√											√	√					
PA (questionnaire)				√														√				√	
Sleep																							
Body composition																							
CRF																							
Muscular strength																							
Bone health																							
Executive function																							
Wellbeing																							
Enjoyment																							
Motivation																							
Affect																							
Self-efficacy																							
Academic assessment	√																			√			

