### Outcome measurements

Outcome measurements will be conducted in the school premises by trained research assistants who will remain blinded to group allocation throughout all assessment time-points. All measurements will be introduced and explained during the training workshop and will be described again prior to the commencement of the measurements to ensure clarity. The measurements will be conducted during their regular PE lessons. Details of the outcome measures are summarised in Table 5.

**Table 5 T5:** How, when and where the outcome variables will be measured.

Outcomes	Tools	Timing	How and where (all participants, measured at class level)
Physical activity	GENEActiv	One week before and after intervention, first and last week of intervention.	A subsample of 60 participants (30 in each group, 30 males) will be randomly selected to wear the GENEActive accelerometer for 14 days consecutively for twice, covering the total 4 weeks.
Cardiorespiratory fitness	20 m shuttle run	T1, T2, T3	Multiple measurement stations will be held, and participants will be split into groups to ensure efficient measurements. Two physical education lessons are estimated to be sufficient. All these measurements will be conducted in sports hall.
Body composition	TANITA	T1, T2, T3	
Muscular strength	Handgrip, standing long jump	T1, T2, T3	
Bone health	GE Achilles	T1, T2, T3	
Executive function	Flanker tasks, visual 2-back tasks, colour-shape switch tasks	T1, T2, T3	Perform the executive function tasks online in a school computer room in one physical education lesson (40 min).
Wellbeing	SDQ	T1, T2, T3	Finish together using one physical education lesson (40 min) in a school computer room with the instruction of research staff.
Enjoyment	PACES	T1, T2, T3	
Motivation	BREQ-2	T1, T2, T3	
Affect	PANAS-SF	T1, T2, T3	
Self-efficacy	PPAS	T1, T2, T3	
Academic performance	End-of-term academic examinations	By the end of term 1 and T2	Obtained directly from head teacher.

SDQ, strength and difficulty questionnaire; PACES, physical activity enjoyment scale; BREQ-2, exercise regulations questionnaire; PANAS-SF, positive and negative affect schedule short form; PPAS, perceived physical ability scale; T1, pre-intervention; T2, immediately post-intervention; T3, 2-month follow-up.

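### The pupil workshop differs by arm, yet the plan places it before baseline testing and before randomisation

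*Protocol article*

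**What the plan says.** Five places in the protocol article bear on the order of events.

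- **Recruitment and allocation:** "The randomisation and allocation will take place after baseline assessment".
- **Table 1 (Study design):** the row "Training workshop" has its tick at term 2 week 2, and the row "Randomisation" has its tick at week 4. The maturity and physical activity questionnaire rows have their baseline tick at week 3. The intervention starts in week 5.
- **Table 2 (Intervention delivery and exercise design):** the pupil workshop is set out by arm. Control pupils receive "1) Introduction of the programme; (2) outcome measurements; (3) familiarisation of executive function tasks; (4) maintain daily life". Intervention pupils receive an introduction, the outcome measurements and "familiarisation of equipment (e.g., HR monitor), executive function tasks and HIIT exercises". A separate lesson trains peer-coaches, whom the same section says are chosen within intervention classes.
- **Outcome measurements:** "All measurements will be introduced and explained during the training workshop and will be described again prior to the commencement of the measurements".
- **Executive function:** the workshop that introduces the executive function tasks is dated one week before the intervention begins.

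**The concern.** A workshop labelled by arm needs the allocation. If it comes before the allocation, one of the stated steps has to give way.

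If Tables 1 and 2 are followed, classes are in effect assigned before T1. One arm has then practised HIIT, and the other has been told to carry on as usual, before baseline is taken. The shuttle run can end when a pupil chooses to stop, so it depends on effort. The wellbeing, enjoyment, motivation, affect and self-efficacy scales are self-reported. Both kinds of outcome can respond to knowing one's arm. Blinded assessors do not prevent that, because it is the pupils who would know.

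If Recruitment and allocation is followed, nobody knows in week 2 which class should get which workshop, and Table 2 cannot be carried out on the Table 1 timetable.

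**Working it through.** This is a question of order, and the plan gives no figure to reproduce.

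**Dates.** Table 1 starts week 1 on 26 February, and Intervention delivery gives the year as 2024. Week w starts 7 × (w − 1) days later:

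| Week | Dates | Event with its tick there |
|---|---|---|
| 2 | 4–8 March | Training workshop |
| 3 | 11–15 March | Maturity, activity questionnaire (T1) |
| 4 | 18–22 March | Randomisation; first accelerometer week |
| 5 | from 25 March | First HIIT week |

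The column reading agrees with fixed points elsewhere: the term 1 academic assessment falls in week 22, and the accelerometer ticks fall in the week before the intervention and its first week.

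**Can the statements hold together?**

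1. Table 2 content differs by arm, so its delivery requires known arms.
2. Arms become known at randomisation, which comes after baseline and is ticked in week 4.
3. From 1 and 2, the arm-specific content must come after baseline.
4. Table 1 starts the workshop in week 2, and Outcome measurements puts it before the measurements.
5. Steps 3 and 4 conflict unless the workshop is in two parts. No section describes two parts.

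**Does the Executive function date resolve it?** One week before the intervention is week 4. A workshop then could follow randomisation, but it disagrees with the week 2 start in Table 1. If T1 testing begins in week 3, it would also put task familiarisation and the explanation of measurements after testing had begun. It is a further conflict to reconcile.

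**How a baseline shift would act.** The Statistical analyses section tests group × time. For T1 to T2 the contrast is (T2 − T1) in the intervention arm minus (T2 − T1) in the control arm. Suppose early knowledge of the arm moves the T1 mean by x in the intervention arm and by y in the control arm, and leaves T2 unchanged. The contrast then changes by y − x. The document gives no value or sign for x or y, so the formula shows the route of a bias and no amount.

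**The case against.** The best defence is that the workshop may be staged. Table 2's timing column gives lengths and no dates, the text speaks of workshops in the plural, and both pupil rows mention two lessons. A common part before T1 and a HIIT part after randomisation would fit. The Executive function date shows that some workshop activity may fall in week 4. An article also condenses scheduling detail.

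Much of this stands as a limit on the point. In the text copy of Table 1, merged cells seem to show only at their left edge, so the week 2 tick may mark a start and not the whole window. Most baseline rows, the shuttle run's among them, show no tick, so week 3 is inferred for them. Neither limit removes the conflict, because a workshop that starts in week 2 still starts before randomisation in week 4. Nor is this mere omission: the article states content, timing and allocation order, and they disagree. Staging is plausible but stated nowhere.

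A reader might go further and infer three things that the document does not support:

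- **That allocation was in fact known in week 2, so that the statement about randomisation is untrue.** No section says so. It follows from only one way of resolving the conflict.
- **That an exact number of days separates workshop and randomisation.** This would treat one tick as the full workshop window.
- **That the bias can be put as a share of the 9-lap improvement cited in Sample size estimation.** Any lap shift would be invented, because nothing links a familiarisation session to laps run.

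**Conclusion.** The contradiction is real. Tables 1 and 2, Recruitment and allocation, Outcome measurements and Executive function cannot all be followed as written. Either arm-specific content precedes allocation and T1, or the workshop cannot run as described.

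What is at risk is the standing of T1 as a pre-allocation baseline for the shuttle run and the self-reported outcomes. It would be too broad to say that every baseline measure is affected: the baseline academic scores come from the end of term 1, before any workshop. The size and direction of any bias are unknown.

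The conclusion rests on reading the week 2 tick as at least the start of the pupil workshop and the week 4 tick as randomisation. It does not depend on the exact week of the shuttle run.

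**What to change.** - **Before T1:** give all eight classes one identical session covering the programme introduction, outcome measurements and executive function tasks.
- **After the last T1 test and after randomisation, before the first HIIT session:** give the HIIT exercises, the equipment, the control pupils' instruction about daily life, and the peer-coach training.
- **Text:** show both sessions in Table 1, align Table 2 and the Executive function date, and state that teachers and pupils do not learn the allocation until T1 is complete. While Table 2 is open, correct its lengths: two lessons are 40 min for controls but 80 min for intervention pupils, and Table 5 gives one lesson as 40 min.

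**Cost.** This is mainly wording and a reordered lesson, but week 4 becomes tight. Weeks 3 and 4 hold 2 × 3 = 6 PE lessons per class. Table 5's T1 battery uses 2 + 1 + 1 = 4, leaving 6 − 4 = 2. If the common part takes 40 min, the intervention part needs 80 − 40 = 40 min, or one lesson, and the peer-coach session needs one more. That fills both. It works only if T1 starts with week 3 and both T1 and randomisation finish early in week 4.

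**One exception to state.** The accelerometer subsample is stratified by group, and its pre-intervention week is week 4. Its first week therefore cannot lie wholly before allocation on this timetable, and the revised text should say how it is handled.
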